# Study of Medical Ultrasound for Rhizarthrosis (SUR): study protocol for a randomized controlled single-center pilot-trial

**DOI:** 10.1186/s13063-020-04375-2

**Published:** 2020-06-01

**Keywords:** Degeneration, Rhizarthrosis, Trapeziometacarpal osteoarthritis, Thumb basal joint arthritis, Thumb carpometacarpal joint arthritis, Hand therapy, Therapeutic ultrasound

## Abstract

**Background:**

Rhizarthrosis (trapeziometacarpal osteoarthritis) is the second most common site of osteoarthritis in the hand affecting 10–30% of adults over the age of 50. Up to four times as many women as men have rhizarthrosis. Clinical symptoms include functional disability of the thumb, pain, joint swelling, and reduced strength. The first carpometacarpal joint is pivotal in the opposition of the thumb and allows a high degree in flexibility to humans. Current therapies focus mainly on surgical strategies, which should be considered in advanced, therapy-resistant stages to relieve pain and improve function. However, conservative treatment methods are urgently required in presurgical stages. The efficacy of conservative treatment options for rhizarthrosis, which are intended to preserve function, joint integrity and to relieve pain, has not been adequately studied. In the clinical study protocol presented here, we investigate the efficacy of multimodal hand therapy versus therapeutic ultrasound versus combination therapy with both hand therapy and therapeutic ultrasound.

**Methods:**

This study is a single-center, randomized, controlled, parallel-group pilot trial. One hundred fifty patients with rhizarthrosis and current disease activity will be randomized to one of three conservative interventions over 6 months. Interventions are (1) multimodal hand therapy (2) therapeutic ultrasound, and (3) combination therapy with both hand therapy and ultrasound therapy. The primary outcome measure is the Disabilities of the Arm, Shoulder, and Hand (DASH) questionnaire score after 6 months. Secondary endpoints are changes in pain, quality of life, disability progression, and changes of hand function. Safety will also be assessed.

**Discussion:**

Clinical data suggest that multimodal hand therapy may improve functionality and reduce pain in rhizarthrosis. Clinical data regarding therapeutic ultrasound are not available. Clinical evidence is lacking. This study is the first clinical study investigating the effects of multimodal hand therapy in direct comparison to therapeutic ultrasound and to a combination therapy with both hand therapy and ultrasound therapy for rhizarthrosis.

**Trial Registration:**

ClinicalTrials.gov; NCT04115085; Registered on September 30, 2019.

## Introduction

Rhizarthrosis (or osteoarthritis of the trapeziometacarpal joint) (OAT) is a common form of osteoarthritis in the hand leading to chronic disability in humans over 50. Although the exact mechanisms of osteoarthritis are still elusive, various person-level risk factors are recognized [1–9]. Although the hand X-ray is the gold standard for diagnosing and monitoring OAT, it has limited correlation to clinical symptoms [2, 10, 11]. The prevalence ranges between 4 and 36% depending on the diagnostic criteria used, rises sharply at ages over 60, and is thought to be twice to four times higher in women [2, 9–13] . OAT leads to articular cartilage damage, adjacent tissue degeneration, and may result in total joint destruction. Moreover, OAT is a major cause of progressive disability, early retirement, and depression in adults [8, 14, 15]. Currently, there is no cure for OAT, but several surgical therapies are available, with or without alloplastic reconstruction, which may improve function und reduce pain [16, 17]. However, they all may have substantial side effects, failure rates, and patients respond differently due to the complex nature of the disease. Therefore, conservative options should be considered first [18]. Consequently, there is a need for conservative therapies such as specific hand therapies that may reduce OAT symptoms, improve the patient’s quality of life, and, at best, delay disease progression [19]. It is unclear which conservative measures, if any, are most effective [20]. The aim of conservative treatment is to restore thumb functionality, including pain relief, stability, motility, and strength. Treatments commonly used prior to surgery include injections (cortisone, hyaluronate), analgesics, patient education in joint protection, strengthening exercises, assistive devices, and orthotics [21, 22]. Few randomized clinical trials on conservative treatment of OAT have been published [22–27]. There is increasing evidence favoring multimodal manual treatment to reduce pain and ameliorate function in OAT patients [26, 28–30]. For more than 60 years, therapeutic ultrasound (TUS) has been a non-invasive method to treat musculoskeletal pain, soft tissue injuries, and chronic wounds with debatable efficacy [31, 32]. However, recently TUS was reported to improve function, tissue regeneration, and relieve pain via thermal and non-thermal mechanisms in osteoarthritis of the knee [33–36]. Experimental data suggest that TUS treatment might prevent degenerative changes of the meniscus and exert a reparative effect via activation of cartilage growth factors [37]. Despite such evidence of efficacy, to the best of our knowledge, TUS has never been studied in OAT. Despite this lack of proven efficacy, based on our clinical experience, physiotherapists frequently use TUS to treat rhizarthrosis. It is of interest that TUS was used as a harmless, non-invasive ‘sham procedure’ in nontherapeutic doses in several clinical studies in OAT [20]. The aim of the present study is (1) to provide a direct comparison of the efficacy of two promising and readily available conservative treatment methods for symptomatic OAT, namely multimodal hand (MHT) therapy and TUS, (2) to suggest treatment recommendations, and (3) to offer direction for future studies. This research is expected to have a positive impact on OAT patients, because if MHT or TUS can reduce pain and improve function of the basal thumb joint, the significant disease burdens associated with pain and psycho-emotional stress, lost productivity, and frequent health care visits will also be reduced.

## Methods

### Study design

This is a single-center, randomized, controlled, repeated-measures, three-armed, parallel-group study conducted at the Waldfriede Hospital Berlin. Recruitment started in October 2019 (ClinicalTrials.gov identifier: NCT04115085). Patients are recruited from our hand surgery outpatient clinic on the Waldfriede Hospital campus. Further recruitment strategies include specific study calls on the website of the Waldfriede Hospital and information events and lectures for patients including distribution of study flyers. We intend to randomize 150 OAT patients to one of three hand therapeutic interventions. Intervention groups are (A) MHT with 18 sessions over 9 weeks, and (B) therapeutic TUS with 18 sessions over 9 weeks, and (C) combination therapy with MHT directly followed by TUS with 18 sessions over 9 weeks. Participants are studied on the first day before the intervention starts and at 9, 13, 17 and 33 weeks after the start of the intervention. The institutional review board of Waldfriede Hospital Berlin gave a positive evaluation for the study and written informed consent was obtained from all participants prior to study entry (Additional files 1 and 2). The study is conducted in accordance with the Declaration of Helsinki in its currently applicable version, the guidelines of the International Conference on Harmonization of Good Clinical Practice (ICH-GCP) and applicable German laws. Table 1 and Fig. 1 show the visit schedule and the study flow chart, respectively. Participants do not receive remuneration. For further details refer to the SPIRIT checklist (Additional file 2).

**Table 1 Tab1:** SPIRIT SUR study schedule

Visit	-1 Screening	0 Baseline Start intervention	1 End of intervention	2 Follow-Up	3 Follow-Up	4 Final follow-up visit
Week	−12 (max)	1	9	13	17	33
Informed consent	x					
Demographics	x					
Inclusion / exclusion criteria	x	x	x	x	x	x
Case history	x					
Medication	x	x	x	x	x	x
DASH		x	x	x	x	x
SF-36		x	x	x	x	x
VAS pain		x	x	x	x	x
Key pinch force		x	x	x	x	x
Goniometry		x	x	x	x	x
MHT		x	x			
TUS		x	x			
MHT + TUS		x	x			
Physical examination	x				x	
AE / SAE query		x	x	x	x	x

*AE* adverse event, *DASH* Disabilities of the Arm, Shoulder, and Hand, *MHT* multimodal hand therapy, *SAE* serious adverse event, *SF-36* Short Form 36, *SPIRIT* Standard Protocol Items: Recommendations for Interventional Trials, *SUR* Study of Medical Ultrasound for Rhizarthrosis, *TUS* therapeutic ultrasound, *VAS* visual analogue scale

**Fig. 1 Fig1:**
[figure not shown]
SUR study flow chart. *SUR* Study of Medical Ultrasound for Rhizarthrosis

### Participants

Patient information and informed consent have been prepared in accordance with the guidelines of the institutional review board of Waldfriede Hospital Berlin. Potential participants receive both forms at least 24 hours before one of the study physicians personally explains all study procedures to them. If he or she is willing to participate and has had sufficient time to ask questions, written informed consent is given. Afterwards, inclusion and exclusion criteria are assessed. Main inclusion criteria are a definite diagnosis of OAT according to the stage I to IV Eaton and Littler X-ray criteria [38] and clinical symptoms in the region of the thumb base for at least 3 months.

#### Complete list of inclusion criteria

Male and female patients aged 40 to 90 yearsPain intensity in the region of the thumb base in pain phases ≥40 mm on the visual analogue scale (VAS) of 0 to 100 mm (relative to the last 24 hours)Complaints for at least 3 monthsX-ray Eaton and Littler stage I–IV determined at least onceAbility to give verbal and written consentHealth insurance

#### Complete list of exclusion criteria

History of surgery on the affected hand, wrist, or forearmPlanned surgery within the next 8 monthsAnticoagulation (Vitamin-K antagonists, heparin)Hemophilia, von Willebrand-Jürgens syndrome, thrombocytopathy, or other blood anomaliesAcute pain medication (< 7 days)Systemic medication with corticoids or immunosuppressantsIntra-articular injections or Radiosynoviorthesis (radiosynovectomy) (RSO) within the last 3 monthsPregnancy, lactationSignificant cognitive impairmentClinically relevant or progressive systemic disease (e.g., liver, kidney, cardiovascular system, respiratory tract, vascular system, brain, metabolism, thyroid) that could affect the course of the studyMalignant diseaseSimultaneous participation in an interventional study or participation in an interventional study in the last 2 months before study inclusionClinically relevant addiction or substance abuse disorder (defined as alcohol or drug abuse)Insufficient mental capacity to cooperateSuspected lack of complianceMedical, psychiatric or other conditions that restrict the patient’s following abilities: to interpret the study information, to give informed consent, to adhere to the rules of the protocol, or to complete the study

Discontinuation criteria are withdrawal of consent, subsequent occurrence of an exclusion criterion, lack of compliance, and medical reasons for stopping the intervention. Participants meeting a discontinuation criterion are offered the chance to attend the remaining study visits for follow-up outside the study protocol.

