### Outcome parameters

Primary outcome is the change in the disease-specific Disabilities of the Arm, Shoulder, and Hand (DASH) questionnaire score after 9, 13, 17, and 33 weeks compared to baseline [41, 42].

Secondary patient-reported outcomes include: (1) VAS pain determined by change in distance between the patient-made mark after 9, 13, 17, and 33 weeks compared to baseline; (2) Short Form 36 (SF-36) determined by scale score change after 9, 13, 17, and 33 weeks compared to baseline [43]. Secondary disease-related outcomes include: (3) Thumb force or key pinch force evaluation, determined by change in Kg after 9, 13, 17, and 33 weeks compared to baseline. All thumb force evaluations will be assessed in the following position: Thumb on top of the radial side of the index finger below. (4) Goniometry measurement determined by change in range of motion after 9, 13, 17, and 33 weeks compared to baseline. All goniometric evaluations assess the active range of motion (ROM) of the angle between the dorsal axis of the thumb and the index finger with a manual goniometer.

All clinical assessments will be performed by the same experienced evaluator at all time intervals, who is blinded to the treatment allocation.

For safety monitoring, patients will be asked for tolerability of the interventions and in case of AEs a medical doctor is always at our site to provide help. For a detailed overview of assessments and endpoints see Table 1.

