### Power calculation

Since this study is planned as a pilot study, formal statistical power calculations are not performed for all measures and tests of interest. The primary limitation for making power calculations is the lack of available information on what would constitute a clinically significant effect size for the measures of interest in OAT. Thus, we refer to other studies (regarding osteoarthritis of the knee and ultrasound therapy) for a “sample size calculation” since there is no justification with regard to statistical power [34, 35, 44]. The parameters determined with this pilot study will be used to plan the number of cases in a subsequent controlled prospective randomized trial. However, we estimated a sample size of 45 patients per group and defined a two-sided significance level of 0.05 for all tests. We expect a dropout rate of approximately 10% and therefore plan to enroll 50 patients per group, or a total of 150 patients.

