### Data analysis

The data collected are described using statistical parameters. Continuous data are described with mean, standard deviation, minimum, maximum and 95% confidence intervals; for categorical data, the frequencies attained and the associated percentages are given with 95% confidence intervals.

The statistical analysis will only include the patients who complete the study in accordance with the protocol. Sub-collectives can be examined exploratively if this makes sense after the survey has been completed. In addition to the primary analysis of the comparison of patients with and without ultrasound therapy, there is a comparison of the patients between the different groups.

Group differences (MHT versus TUS versus study group with MHT + TUS) regarding the primary endpoint are analyzed with the non-parametric Kruskal-Wallis test for independent samples. After the global test, the groups are compared in pairs (Mann-Whitney tests). Secondary endpoints are evaluated according to the scaling of the data but are also always tested non-parametrically. The evaluation of intra-group differences (DASH or other characteristics after 9, 13, 17, and 33 weeks) is carried out by means of a nonparametric analysis of variance for repeated observations (Friedman test). In line with the nature of the pilot study, no adjustment is made for multiple testing. A *p* < 0.05 is considered (in the exploratory sense) to be statistically significant. Missing values will be replaced using multiple imputation [45]. All occurring AEs (AEs and SAEs) are described individually.

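### Patients who meet an exclusion criterion after randomisation leave protocol follow-up and the analysis, a loss likely to fall disproportionately on poor responders

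*Protocol article*

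**What the plan says.** The rule stands in the Protocol article directly below the exclusion criteria: "Discontinuation criteria are withdrawal of consent, subsequent occurrence of an exclusion criterion, lack of compliance, and medical reasons for stopping the intervention". The exclusion list above it includes acute pain medication, systemic corticoids or immunosuppressants, recent intra-articular injection or radiosynoviorthesis, planned surgery and suspected lack of compliance. It also includes pregnancy, malignancy, anticoagulation, blood disorders and participation in another trial.

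The next sentence covers what follows: "Participants meeting a discontinuation criterion are offered the chance to attend the remaining study visits for follow-up outside the study protocol".

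In Table 1 (Study design), the row "Inclusion / exclusion criteria" is marked at screening, baseline and weeks 9, 13, 17 and 33. The Medication row is marked at the same visits.

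The primary outcome is the change in the DASH "questionnaire score after 9, 13, 17, and 33 weeks compared to baseline". On the analysis set, Data analysis says: "The statistical analysis will only include the patients who complete the study in accordance with the protocol". Later in the same section: "Missing values will be replaced using multiple imputation". No sentence brings discontinued patients back into the analysis.

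**The concern.** The rule does not distinguish stopping the intervention from leaving the study. A patient whose thumb does badly may start an analgesic, have an injection or be listed for surgery. Each of these events matches an exclusion criterion and so triggers discontinuation. The Introduction itself names injections and analgesics among the treatments commonly used before surgery. Lack of compliance is a matter of judgement, and the study is open-label.

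Treatment ends at week 9, but the rule continues to week 33. In that later period it stops no study treatment and only removes outcome data from the trial. The last visit is the most exposed, because removals accumulate.

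If removal is related to response, the arms compared at the end are selected groups rather than the randomised ones. The pilot is meant to supply the parameters for a later trial, and the Introduction also aims at treatment recommendations. A distorted difference would affect both.

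**Working it through.** **1. The plan's own figure.** Power calculation: "we estimated a sample size of 45 patients per group and defined a two-sided significance level of 0.05 for all tests", with about 10% dropout. 45 / (1 − 0.10) = 50 per group, and 3 × 50 = 150, as stated. The allowance replaces numbers (150 × 0.90 = 135 completers). It does nothing about which patients are lost.

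**2. The route out of the analysis.**
- A later exclusion criterion or non-compliance leads to discontinuation (text below the exclusion list).
- Discontinuation leads to optional visits outside the protocol (next sentence).
- Only patients who complete according to protocol are analysed (Data analysis).
- Multiple imputation, as written, fills gaps within that analysed set. It is not said to cover patients outside it.

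**3. Timing.** 33 − 9 = 24 weeks of follow-up lie after the treatment course. This is calendar time. The article does not say how many discontinuations would fall there.

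**4. Size when removal follows response.** None of these inputs is in the article: DASH change standardised to SD 1 with improvement positive, true difference d = 0.5, and one removal threshold c common to both arms, set so that 10% are removed overall. A removal index has correlation ρ with response, and patients below c are removed. If a share q of an arm is removed, the mean of those kept rises by ρ·λ(q), where λ(q) = φ(z_q) / (1 − q), z_q is the normal quantile of q and φ is the normal density.

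| ρ | Removed, better arm | Removed, worse arm | Difference among those kept |
|---|---|---|---|
| 1 | 5.8% (λ = 0.123) | 14.2% (λ = 0.262) | 0.5 + 0.123 − 0.262 = 0.36 |
| 0.5 | 7.8% (λ = 0.159) | 12.2% (λ = 0.230) | 0.5 + 0.5 × (0.159 − 0.230) = 0.46 |

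A simulation with 1,000,000 patients per arm gave 0.359 and 0.462. With ρ = 1, overall removal of 5% leaves about 0.41 SD and of 30% about 0.25 SD. The effect is attenuation: the worse arm loses more of its poor responders and so looks better than it is.

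**5. Size when there is no true difference.** If removal depends only on response and the arms do not differ, the removal rates are equal and the bias is zero. A spurious difference needs unequal rates imposed by something else, such as unequal open-label judgement or use of other treatment. It then equals ρ × [λ(q₁) − λ(q₂)]. The type I error below comes from simulation with 50 randomised per arm, a Mann-Whitney test and ρ from 0.5 to 0.8.

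| Removed (assumed) | λ(q₁) − λ(q₂) | Spurious difference | Type I error |
|---|---|---|---|
| 15% vs 15% | 0 | 0 | about 5% |
| 13% vs 7% | 0.243 − 0.144 = 0.099 | 0.05 to 0.08 SD | about 6 to 7% |
| 20% vs 6% | 0.350 − 0.127 = 0.223 | 0.11 to 0.18 SD | about 8 to 14% |

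The 13% versus 7% row averages to the protocol's own 10% dropout.

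**The case against.** - **The visits are offered.** The data may therefore be collected, and Data management says that participants are asked whether their data may be used if they withdraw. This stands against any claim that the scores are never obtained. It does not answer the point: attendance is voluntary, the visits are placed outside the protocol, and the analysis set leaves these patients out.
- **Most criteria have no link to the thumb.** Pregnancy, malignancy, anticoagulation and others are unrelated to response, and analgesics or corticoids may be taken for another condition. This stands. A reader might infer that the rule removes exactly the treatment failures. The list supports only a disproportionate loss of poor responders.
- **Table 1 is indirect evidence.** Its row joins inclusion and exclusion criteria and states no consequence. Only the discontinuation sentence does. The table shows that checks are scheduled to week 33, and no more.
- **Inflated false positives.** A reader might infer that the rule raises the type I error as such. It does so only under unequal removal unrelated to response, and no passage supports such rates.
- **Most removals fall after treatment.** A reader might infer this from 24 of 33 weeks, but that is a share of time, not of events. Non-compliance and medical stopping belong naturally to the nine treatment weeks.
- **It is a pilot with exploratory p-values, and the point overlaps with the completers-only set.** Both are fair and lower the severity. The overlap is not complete: widening the analysis set cannot recover a week 33 score from a patient who was only invited to an optional visit outside the protocol.

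**Conclusion.** The concern holds as a stated design choice, not as an omission. Followed as written, the plan drops patients from protocol follow-up and from the analysis for reasons that in part plausibly reflect poor response, and it goes on doing so after treatment has ended.

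The size and direction of the bias cannot be derived from the article. The illustrations rest on assumed removal rates, an assumed effect and an assumed link between removal and response. On those terms the main harm is attenuation, with 0.5 SD falling to about 0.36 to 0.46 SD at 10% overall removal. A false-positive excess is conditional, and it is small at rates near the planned dropout. This should be fixed, and handled together with the completers-only analysis set.

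**What to change.** - Separate stopping the intervention from leaving the study. Make the assessments at weeks 9, 13, 17 and 33 trial visits for every randomised patient unless consent to follow-up is withdrawn.
- Include those data in a main analysis of all randomised patients, and keep the completer analysis as a sensitivity analysis.
- Record the event that triggered discontinuation, using the Medication query already made at each visit where it applies, and report it by arm.
- Leave the rules for stopping treatment and the scheduled criteria checks as they are. The statistical problem does not require changing either.

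The cost is a short amendment and slightly more follow-up of patients who are already offered these visits. Enrolment stays at 150, and the number analysed moves from about 135 towards 150. The amendment protects only visits still to come, so its value falls with delay.
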